## Stopping Criteria

If any subject experiences a serious adverse event, that in the judgment of the Principle Investigators and/or the Medical Director of Protalix Ltd. is life-threatening and definitely related to study medication (see Section 7.2), the study will be stopped

## Study Flow Chart

See Appendix 1

# SUBJECT POPULATION

## Inclusion Criteria

The following are the inclusion criteria:

1. Healthy male or female between 18 and 45 years of age.
2. Female subjects must agree to use a medically acceptable method of contraception at all times during the study and must have a negative serum pregnancy test at baseline and during the study period.
3. Females of child-bearing potential must be non-pregnant and not lactating and using adequate birth control such as oral contraceptives
4. Negative laboratory tests for HIV, HBsAg or HCV
5. Naïve to any previous recombinant protein therapy
6. Provide written informed consent
7. Have the ability to understand the requirements of the study and to comply with the study protocol and dosing regimen

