**PROTOCOL SYNOPSIS**

**Protocol Number:** P-01-2005

**Title:** A Phase I, Non-Randomized, Open Label, Single Dose, Dose-Escalation Safety Study of Recombinant Human Glucocerebrosidase (prGCD) in Healthy Volunteers

**Study Phase:** 1

**Study Site:** Jerusalem Phase I unit, Hadassah Medical Organization, Jerusalem, Israel

**Test Material:** human prGCD 15 units/kg; 30 units/kg; 60 units/kg and vehicle

**Dose:** human prGCD will be administered as an intravenous infusion (IV) delivered over 1.5 hour. The rate of infusion is to be 135 mL/1.5 hr (1.5ml/minute). The infusion rate will be the same over 90 minutes for all doses. All subjects will receive all doses in a sequential manner starting with vehicle. Subjects will be closely monitored for 2 hours from the time of the initiation of the infusion.

Vehicle will be given at the baseline visit. The initial human prGCD dose of 15 units/kg will be given at Day 8; 30 units/kg dose will be administered on Day 15, and 60 units/kg dose on Day 22.

**Route of Administration:** Intravenous (IV)

**Controls:** Each subject will receive vehicle and thereby will be his/hers own control.

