# STUDY DESIGN

The proposed investigation will be a phase I, single-center, non-randomized, open label, safety study of three single escalating doses of human prGCD administered as an intravenous infusion (IV) to six healthy volunteers. Subjects meeting the entry criteria will be eligible to receive study drug. Urine will be collected 24 hours prior to screening to assess renal function. Seven visits are scheduled for this study: pre-screening (Day -1), Screening (Day 0), baseline (Day 1), Visit 1 (Day 8), Visit 2 (Day 15), Visit 3 (Day 22) and follow-up visit (Day 29). The study procedures for each visit are presented in the study flow chart (Appendix 1). The duration of study is 29 days.

Subjects will be monitored over 24 hours from the commencement of the infusion of each dose at the Hadassah medical center, Phase I unit. The treatment will consist of a single dose infused for 1.5 hours (1.5mL/min). The infusion rate may be adjusted according to subject symptoms and signs: slower rate (1mL/min) upon adverse effect or faster (2mL/min.) upon lack of any symptom and signs. The vital signs for each subject will be monitored during infusion. ECG will be done at baseline and at 8 hours following the infusion. Subjects will remain at the clinic for 8 hours post-infusion and will be discharged if no AEs are observed. Subjects will return to the clinic 24h post initiation of infusion for additional safety assessment. Vital signs will be recorded during the infusion and PK sampling every 30 minutes (up to 3.5 hrs), and afterward at 8 and 24hrs post infusion.

Each subject will receive a single IV dose of vehicle at the baseline visit (Day 1). Blood samples for PK will be collected prior to dosing (0) and at 5, 45, 80 and 90 minutes during the infusion and 100, 115, 130, 150, 180, 210 minutes and 24 hours from initiation of infusion. On Day 8, subjects will receive a single 15 units/kg of study drug and will have the same blood samples taken as per Day 1. On Day 15, subjects will receive a single 30 units/kg of study drug and have the blood samples taken as per Day 1. On Day 22, subjects will be administered a single dose of study drug of 60 units/kg, and have the same procedures performed as Day 1.

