## Screening Visit (Day 0), Screening Visit can be done 21 day before planned visit.

1. Investigator will review all inclusion and exclusion criteria and determine subject's eligibility
2. Informed consent is signed
3. Demographics (date of birth, gender, ethnic origin)
4. Medical history (including concomitant medication use and medical conditions)
5. Complete physical examination including vital signs (blood pressure and heart rate), body weight (kg) and height (cm)
6. Chest X-ray (if not obtained within the past 6 months prior to study start), if an Chest X-ray was done within the past 6 month the film must be available for reading by the PI
7. Electrocardiogram (ECG)
8. Withdrawal of 22 mL venous blood for laboratory tests, which include,:
   1. Serum chemistries including electrolytes (K, Na, Cl, HCO3, Ca, and P), liver function tests (AST, ALT, LDH, AlkP, GGT, and Bilirubin), Renal function tests (BUN, and Creatinine,) CPK, Serum proteins(Albumin,Globulin), Cholesterol, and Uric Acid
   2. Complete blood cell count including white blood cells differential count (CBC), and coagulation profile (PT, PTT)

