   3. ANF, ESR, C3
   4. Serology: HBsAg, HCV and HIV
   5. Serum pregnancy test
9. Subjects failing to meet the entry criteria will be consider screening failures. A screening log, containing the screening number, subject’s initials and reason(s) for failure, is to be maintained by the investigator in the study files.

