## Baseline Visit (Visit 1-1a, Day 1-2, Treatment visit) Baseline Visit can be done ± 1 day from planned visit.

1. Baseline data will be collected at time 0 immediately prior to infusion of study medication and at 24h (baseline a) from initiation of infusion.
2. Body weight, vital signs and physical examination.
3. Concomitant medications
4. Electrocardiogram (ECG) (will be performed only at time 0 and 8hr post infusion.)
5. Withdrawal of 22 mL venous blood for laboratory tests, pre infusion (time 0) and 24h post infusion which include:
   1. Serum chemistries including electrolytes (K, Na, Cl, HCO3, Ca, and P), liver function tests (AST, ALT, LDH, AlkP, GGT, and Bilirubin), Renal function tests (BUN, and Creatinine,) CPK, Serum proteins(albumin and globulin), Cholesterol, and Uric Acid
   2. Complete blood cell count (CBC), and coagulation profile (PT, PTT)
   3. ANF, ESR, C3 (C3 test should be done both at time 0 and 24hr post infusion)
6. Urinalysis
7. 5mL PK blood for plasma sample prior to dosing
8. Prepare drug (vehicle) for infusion (see Section 6.5)
9. Administer the investigational drug (see Section 6.2) and monitor safety as described below:

| Parameters | Pre-infusion | During and Post-infusion |
| --- | --- | --- |
| Temperature | + | +a |
| Blood Pressure | + | +a |
| Pulse Rate | + | +a |
| Respiratory Rate | + | +a |

a Vital signs will be measured prior to infusion and every 30 minutes during infusion and at 8, 24 hours post infusion

1. Withdrawal of 5 ml blood for plasma samples at 0,80, 210 minutes and 24 hours post-infusion.
2. Withdrawal of 5ml blood for serum for antibody detection and characterization at 24h post infusion
3. Adverse events

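### Criterion 2 asks for a negative pregnancy test at baseline, but the test is scheduled only at screening and Day 29: either the Day 1 test is missing or the criterion names the wrong visit, and on both readings no test is repeated before any infusion

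*Protocol*

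**What the plan says.** Section 4.1, criterion 2, states that female subjects "must have a negative serum pregnancy test at baseline and during the study period".

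The protocol treats baseline as a named visit on Day 1:

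- Synopsis, Dose: "Vehicle will be given at the baseline visit".
- Section 3 lists it after, and apart from, Screening (Day 0): "baseline (Day 1), Visit 1 (Day 8), Visit 2 (Day 15), Visit 3 (Day 22) and follow-up visit (Day 29".
- Section 5.3 is headed "Baseline Visit (Visit 1-1a, Day 1-2, Treatment visit").
- Appendix 1 has one column for Screening and another for Visit 1 (Baseline).

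Eligibility is checked at screening, where Section 5.2 says "Investigator will review all inclusion and exclusion criteria". The "Serum pregnancy test" is on the laboratory list of that visit. The heading of Section 5.2 also allows an early visit: "Screening Visit can be done 21 day before planned visit". The test appears once more, in the Day 29 list of Section 5.5.

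The Day 1 laboratory entry in Section 5.3 reads "Withdrawal of 22 mL venous blood for laboratory tests, pre infusion (time 0) and 24h post infusion which include". It goes on to name chemistries, blood count, coagulation, ANF, ESR and C3. Neither that list nor the one in Section 5.4 for Days 8, 15 and 22 includes a pregnancy test.

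**The concern.** A site that follows Section 5.3 and the flow chart will do no pregnancy test on Day 1. Anyone who then reads criterion 2 with the protocol's own visit labels would find that requirement unmet for every woman enrolled. The two parts of the protocol cannot both be followed as written.

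Behind the wording lies a question of subject safety. Day 1 is vehicle only, so the exposure at issue is the three active doses. A pregnancy that begins after screening, or is too early to detect at screening, would not be found by any scheduled test until Day 29. By then all three active doses have been given. Section 1.1 describes this as the first trial of the plant-cell product. The subjects are healthy volunteers aged 18 to 45 of either sex, and pregnancy is an exclusion under Section 4.2.

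**Working it through.** The protocol states no figure on this point, so there is none to reproduce. The check compares the requirement with the schedule and then counts days.

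**Step 1: where the test is scheduled**

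| Visit | Infusion | Test in the visit list (Sections 5.2 to 5.5) | Test in Appendix 1 |
|---|---|---|---|
| Screening (Day 0) | none | yes | yes |
| Day 1 | vehicle | no | no |
| Day 8 | 15 units/kg | no | no |
| Day 15 | 30 units/kg | no | no |
| Day 22 | 60 units/kg | no | no |
| Day 29 | none | yes | yes |

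The visit lists and the flow chart agree with each other, so the gap is not an artefact of a broken table. The mismatch is with criterion 2.

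**Step 2: age of the latest result at each infusion**

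Age = infusion day minus day of the latest test. The inputs are the infusion days (synopsis, Design), screening on Day 0 (Section 3) and the 21-day allowance (Section 5.2). The planned visit from which the 21 days run is not defined. Counting back from Day 0 puts screening on Day -21 and gives the upper bound. Counting back from Day 1 takes one day off each figure.

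| Infusion | Screening on Day 0 | Screening on Day -21 | With a Day 1 test added |
|---|---|---|---|
| Day 1, vehicle | 1 - 0 = 1 | 1 + 21 = 22 | 1 - 1 = 0 |
| Day 8, 15 units/kg | 8 - 0 = 8 | 8 + 21 = 29 | 8 - 1 = 7 |
| Day 15, 30 units/kg | 15 - 0 = 15 | 15 + 21 = 36 | 15 - 1 = 14 |
| Day 22, 60 units/kg | 22 - 0 = 22 | 22 + 21 = 43 | 22 - 1 = 21 |

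The ±1 day visit windows move each figure in the two screening columns by a day. In the last column both visits can move. The ranges at the active doses become 7 - 2 = 5 to 7 + 2 = 9, 14 - 2 = 12 to 14 + 2 = 16, and 21 - 2 = 19 to 21 + 2 = 23 days. With a test before each infusion the age is about 0 days.

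The next scheduled test comes 29 - 22 = 7 days after the highest dose.

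**Step 3: number of added tests**

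The trial has six subjects, and the number of women is not fixed. Day 1 adds at most 6 × 1 = 6 tests. Days 8, 15 and 22 add at most 6 × 3 = 18. The total is at most 24.

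**The case against.** The strongest reply is that no test is missing and one word is loose. Consent and the eligibility review take place only at screening, an inclusion criterion is applied there, and the test is done there. The protocol also uses the word baseline loosely elsewhere. Section 3 places an ECG at baseline and again 8 hours after infusion, although ECGs are done at every infusion visit. Section 5.4 speaks of baseline data immediately before each later infusion. This stands in part: the documents do not settle which text is in error. It does not remove the mismatch, because no section calls the screening visit baseline. On this reading criterion 2 itself needs correcting.

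The second reply is that pregnancy is guarded against in other ways: contraception throughout (criteria 2 and 3), the exclusion of pregnant women, physical examination at each infusion visit, review of results before each escalation (Section 3), questioning about symptoms (Section 7.3) and withdrawal in the subject's interest (Section 8). These lower the risk, but none is a scheduled pregnancy test.

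Third, the Day 1 test alone gains little on the nominal schedule: the result at the first active dose would be 7 days old and not 8. This is correct. The Day 1 test gains more when screening is early, where 29 days falls to 7.

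A reader might also infer that criterion 2 requires a test before every infusion, so that the schedule breaches it on Days 8, 15 and 22 as well. The text does not support this. The criterion asks for a test during the study period without saying when, and the Day 29 test literally meets that.

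**Conclusion.** The mismatch is real and should be fixed before enrolment. Criterion 2 and the schedule disagree about Day 1, and either one may be the text in error. It would go too far to say that a Day 1 test was certainly intended and forgotten. It would also be wrong to say that women are dosed without any test, because the screening test precedes every infusion.

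On either reading no test is repeated before an active dose. The latest result is then 8, 15 and 22 days old nominally, and up to about 29, 36 and 43 days old. The second set is an upper bound: it assumes that the whole 21-day allowance is used and counted back from Day 0. More frequent testing is a safety recommendation and not a contradiction in the protocol.

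The scale is small. At most six subjects are concerned, possibly no women among them, and the chance of an undetected pregnancy cannot be derived from the protocol. No endpoint or analysis is affected.

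**What to change.** 1. **Resolve the mismatch.** Add a serum pregnancy test for female subjects to Section 5.3 and to the Visit 1 column of Appendix 1. Use a pre-infusion sample taken on arrival, early enough for a negative result to be read before the infusion starts. A sample drawn at time 0 itself is too late, since Section 5.3 places time 0 directly before the infusion. Reword criterion 2 to: *negative serum pregnancy test at screening and before the Day 1 infusion*. Name the day in the text, because Section 3 calls Day 8 Visit 1 while Section 5.3 and Appendix 1 give that number to Day 1. If only screening was meant, replacing the word baseline in criterion 2 removes the mismatch but leaves the age of the result unchanged.
2. **Recommended as a safety improvement.** Add a urine or rapid serum test on pre-infusion samples on Days 8, 15 and 22, in Section 5.4 and Appendix 1. Put the rule not to dose after a positive result in the dosing section or in Section 8. It does not belong in the inclusion criteria, since later tests cannot be judged at enrolment.
3. **Keep the Day 29 test** as follow-up.

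The cost is protocol wording, at most 6 routine tests for the first change and 18 for the second, and a short wait before each infusion. Blood and urine are already collected at these visits, so no extra visit is needed. If the laboratory sample must stay at time 0, the Day 1 serum test would need its own draw on arrival; urine avoids this at the later visits.

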## Exclusion Criteria

Subjects will be excluded from the study if they:

1. Have clinical evidence of any active significant disease that could potentially compromise the ability of the investigator to evaluate or interpret the effects of the study treatment on safety assessment and thus increase the risk to the subject to unacceptable levels.
2. Are pregnant or nursing.
3. Presence of any acute or chronic diseases
4. Have a history of any allergies
5. Have been exposed to long-term steroid treatment
6. Had a major operation in last 6 months
7. Have ever been exposed to any previous recombinant protein therapy
8. Have received immuno-suppressive treatment
9. Have a positive HIV, HBsAg and HCV laboratory result
10. Use any medication in cases of chronic drug administration other than vitamins or oral contraceptive (for female).
11. Have participated in another clinical trial during the previous 3 months
12. Have history of alcohol or drug abuse
13. Are considered by the Investigator to be unsuitable candidate for this study

# STUDY PROCEDURES AND VISIT SCHEDULE

## Pre-Screening Visit (Day -1), Pre-Screening Visit must be performed 24 hr before Screening visit

Urine collection 24 hours prior to screening visit to assess renal function

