5. A statement that significant new findings developed during the course of the research, which may relate to the subject’s willingness to continue participation, will be provided to the subject.
6. The approximate number of subjects involved in the study. A subject must give his written consent to participate in the study. This consent must be witnessed and dated and retained by the investigator as part of the study records.

Additional Information and Procedures:

Protalix Ltd. must review and approve the proposed consent form prior to submission to the IRB. The proposed consent form must contain all appropriate elements of consent as outlined in this section.

The principal investigator or designee is responsible for obtaining written informed consent from potential subjects prior to entry into the study. If a subject is incompetent and unable to give consent, then consent must be obtained from the subject’s legal guardian. The investigator must keep each subject’s signed consent form on file for inspection. A copy of the signed document must be given to the subject.

A properly executed, written informed consent in compliance with Food and Drug Administration (FDA) and Good Clinical Practice (GCP) guidelines and the Declaration of Helsinki shall be obtained from each subject prior to entering the study or performing any unusual or non-routine procedure that involves a risk to the subject. A copy of the informed consent document to be used will be submitted by the investigator to IRB for review and approval prior to the start of the study. The investigator shall provide a copy of the signed informed consent to the subject, and a copy shall be maintained in the subject's medical record. Attention is directed to the basic elements that are required to be incorporated into the consent form. Additional elements of informed consent, if appropriate, must be provided to the subject.

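### The protocol schedules a study urine collection on Day -1 but informed consent only on Day 0, contrary to the most natural reading of its own consent rule

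*Protocol*

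**What the plan says.** The urine collection is placed before screening in three parts of the protocol, all in agreement.

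- **Section 3 (Study Design)** lists the visits: "Seven visits are scheduled for this study: pre-screening (Day -1), Screening (Day 0), baseline (Day 1", and so on to Day 29. The same paragraph states: "Urine will be collected 24 hours prior to screening to assess renal function".
- **Section 5.1** fixes the timing in its heading, "Pre-Screening Visit must be performed 24 hr before Screening visit", and gives the visit one task: "Urine collection 24 hours prior to screening visit to assess renal function".
- **Appendix 1** marks urine in the Day -1 column, with a footnote repeating the purpose. The informed consent row has one mark, under Screening, Day 0.

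Consent is item 2 of the screening visit in **section 5.2**: "Informed consent is signed". The heading of that section adds a window: "Screening Visit can be done 21 day before planned visit".

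The governing rule is in **section 10.4**. The principal investigator or designee "is responsible for obtaining written informed consent from potential subjects prior to entry into the study". A later paragraph of the same section repeats that consent precedes entering the study, or precedes any out-of-the-ordinary procedure that carries risk.

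**The concern.** The only activity at the pre-screening visit is a collection made for this study, and it comes before the subject has agreed to take part. If section 10.4 means what it most naturally says, the schedule and the consent rule cannot both be followed. A site that keeps to the visit table departs from the consent rule. A site that takes consent first departs from the visit table.

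What is at stake is subject protection and a clean consent record. The sample is non-invasive, so the physical risk is small. The sequence is nevertheless written into the schedule and would apply to every person who goes through pre-screening, including those who later fail screening.

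**Working it through.** No sample size, power or error rate is involved, so the check is one of sequence.

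**Step 1: order of events.**

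| Event | Day | Where stated |
| --- | --- | --- |
| Urine collection | -1 | Sections 3 and 5.1, Appendix 1 |
| Informed consent | 0 | Section 5.2 item 2, Appendix 1 |

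Gap: 0 - (-1) = 1 day, with the urine first.

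**Step 2: does the screening window change the order?** Let screening fall on day s. Section 5.1 ties pre-screening to 24 hours earlier, so the urine falls on day s - 1 and consent on day s. The gap is s - (s - 1) = 1 day for every s. Using the 21-day window moves both events together and leaves the order unchanged.

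**Step 3: does the result depend on the type of urine collection?** The text says the urine is collected 24 hours before screening. That could mean a sample taken at that time or a timed collection running over the 24 hours. In the first case the procedure is finished before consent; in the second it begins before consent. The conflict is present either way.

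**Step 4: is there consent elsewhere?** Section 5.1 lists none, Appendix 1 has no consent mark at Day -1, and section 10.4 describes no separate pre-screening consent.

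**Step 5: compare with the rule.** Section 10.4 has two limbs.

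- *Entry into the study.* The rule is addressed to potential subjects, that is, people not yet enrolled, and section 3 counts pre-screening as a visit of this study. Section 5.2 also puts consent ahead of demographics, history, examination, chest X-ray, ECG and blood tests, all of which come before enrolment. The protocol therefore treats consent as due before study screening procedures. The Day -1 urine is the one such procedure left outside that arrangement.
- *Out-of-the-ordinary procedure carrying risk.* Urine collection carries little risk, so this limb is not clearly engaged.

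The conflict rests on the first limb alone.

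**Step 6: number affected.** All 6 planned subjects, plus any screening failures who attended Day -1. The protocol gives no expected number of screening failures.

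**The case against.** The best defence is that entry means enrolment once eligibility is established. Sections 3 and 5.2 both use the word in the phrase entry criteria: in section 3, meeting them makes a subject eligible for study drug, and in section 5.2, failing them makes a screening failure. On that usage, entry follows screening and a Day -1 sample does not literally break section 10.4. The protocol does not define entry, so this reading is possible. It is the weaker one, because section 10.4 speaks of potential subjects and section 5.2 already puts consent before the other screening procedures. The uncertainty does mean that the point is a conflict with the most natural reading, not a proven breach.

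A reader might also infer more than the documents support:

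- **That the only quantitative renal baseline is at risk.** It is not. BUN and creatinine are measured at screening (section 5.2) and before the vehicle infusion on Day 1 (section 5.3), and urinalysis is marked at both visits in Appendix 1. Section 5.3 takes baseline at time 0 on Day 1, and no matching post-dose collection is set against the Day -1 urine.
- **That a timed 24-hour collection would be lost.** A timed collection is plausible for renal function but is not stated outright.
- **That the sample could not be recovered.** It could be repeated after consent and before any infusion. Day 1 is itself vehicle only, and the first prGCD dose is on Day 8.
- **That the data would have to be excluded.** The protocol contains no such rule.
- **That section 5.2 wrongly determines eligibility before consent.** Eligibility review is item 1 and consent item 2, but eligibility under section 4.1 includes written consent and negative serology, which come later in the same list. Item 1 cannot be completed first, so the list is not strictly chronological. Its order is at most an editorial matter.

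**Conclusion.** The point holds as a conflict between the visit schedule and the consent rule. Sections 3 and 5.1 and Appendix 1 put a study-specific urine collection on Day -1. Section 5.2 and Appendix 1 put consent on Day 0. No earlier consent is provided for, and section 10.4 is most naturally read as requiring it. The procedure precedes consent by about 24 hours for all 6 subjects and for any screening failure who attended pre-screening.

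This rests on two assumptions: that entry in section 10.4 covers a listed study visit, and that the Day -1 urine is collected for the study and not as routine care. The protocol supports both but defines neither expressly.

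The matter should be corrected because it concerns subject protection and the remedy is simple. No endpoint, estimate, safety comparison or other statistical result depends on it.

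**What to change.** 1. In section 5.1, add informed consent as the first item of the pre-screening visit, to be completed before any urine is collected.
2. In Appendix 1, mark informed consent in the Day -1 column.
3. Amend section 5.2 to match, for example by replacing the signing of consent with confirmation that consent was signed at pre-screening. Placing that item ahead of the eligibility review would be an optional editorial tidying.

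The cost is a wording change, with consent taken at a visit already in the schedule. No visit or sample is added and no analysis changes.
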